## Abstract

**Background:** Diabetic retinopathy (DR) is one of the most common and severe microvascular complications of diabetes mellitus (DM), which results in blindness among adults worldwide. Presently, the efficacy of drug treatments for diabetic retinopathy (DR) is not satisfactory, thus urgently necessitating effective drug treatment measures. TangWang prescription (TWP) has been found to have retinal protection effects in previous clinical and basic research. However, there is a lack of rigorous, randomized, and controlled studies. This study aims to evaluate the efficacy and safety of TWP in delaying the development of DR.

**Methods:** This study is a randomized, double-blind, placebo-controlled, parallel-group, multicenter clinical trial, consisting of 384 participants to be randomized in a 1:1 ratio in the treatment and control groups. Furthermore, the treatment and control groups will be administered the TangWang prescription and the placebo, respectively, each at a dose of one bag twice a day. The study period will last for 48 weeks. The primary outcome measure will be the changes in the degree of retinal microvascular lesions before and after treatment. The secondary outcome will be changes in the degree of hemangioma, microvascular bleeding, microvascular leakage, macular edema, and vision. All statistical tests will be two-sided, and a *p* < 0.05 will be considered statistically significant.

**Discussion:** We hypothesize that the patients with DR will benefit from TangWang prescription, and in addition to the central random system and platform of dynamic information collection, the patients’ conditions will be monitored, and the data collected for analysis. If successful, this study will provide evidence that the TWP formulation delays in the progression of DR.

**Trial registration:** The design of this trial has been registered with the ClinicalTrials.gov (NCT03025399).

## Introduction

Diabetic retinopathy (DR) is one of the most common and severe microvascular complications of diabetes mellitus (DM). In 2020, according to global estimations, the prevalence of DM was 8.3% (International Diabetes Federation, 2019) while that in China was 11.6% in adults, and the number of patients was over 113 million, with the highest-ranking worldwide (Xu et al., 2013). Furthermore, DR shows an increasing trend yearly with DM (Wang et al., 2009; Varma et al., 2016). Several epidemiological studies have found that with a DM duration of 3, 5, 10, and 15 years, the incidence of DR was 8, 25, 60, and 80%, respectively (LeCaire et al., 2013; Azad et al., 2014; Chew et al., 2014; Raman et al., 2016). As for vision-threatening diabetic retinopathy, an estimate of the prevalence rate in global was 10.2% (28 million people) (Zhang et al., 2010). Eye diseases and the visual impairment due to DR have a wide range of effects, including the increase in the financial burden of patients, the decline in work capacity, and the sharp increase in the demand for social support (Coyne et al., 2004).

Glycemic control is the key modifiable risk factor associated with the development of diabetic retinopathy. The International Diabetes Control and Complications Study and United Kingdom Prospective Diabetes Study show that glycemic control effectively delays the occurrence and development of microvascular complications in type 2 DM (T2DM) (Intensive blood-glucose control UKPDS 33, 1998; Nathan et al., 1993). Moreover, blood pressure, blood lipid, pregnancy, inflammatory markers, and body mass index are important risk factors for the development of DR (Frank, 2004; Baker et al., 2016). On the top of control these risk factors, early detection, early diagnosis and early treatment are the key to preventing permanent retinal damage and even blindness caused by diabetic retinopathy. However, for nonproliferative diabetic retinopathy, depending on the severity of the diabetic retinopathy and the presence or absence of macular edema, the treatment decision is whether or not to opt for laser therapy. Panretinal photocoagulation (PRP) is not recommended for DR without macular edema, and the ETDRS study showed that early PRP was more likely to progress to moderate vision loss than delayed photocoagulation (Fong et al., 1999). Early PRP photocoagulation of NPDR showed adverse effects on vision and reduced visual field. For the early stage of DR (non-proliferative stage), the treatment options for these patients are very limited, and the clinical outcomes remain unsatisfactory (Stamper et al., 1978; Haritoglou et al., 2009).

In recent years, the medical management of diabetic retinopathy using Chinese medicine has been cause for concern. Pharmacological researches show that Chinese medicine exerts its neuroprotective functions by inhibiting cell apoptosis in diabetic retinopathy rats and antioxidizing reaction in the retinal tissue of diabetic rats (Liu et al., 2003; Zhang et al., 2018). TangWang prescription (TWP) is composed of five Chinese herbal medicines (Milkvetch root, Radix Salviae Miltiorrhizae, Cattail pollen, Cassia Twig, Pale Butterflybush flower). Previous studies have demonstrated that TWF formula can significantly protect the blood-retinal barrier (BRB), improve endothelial dysfunction and pathological morphology of the pancreas, as well as significantly reduce the positive expression of glucagon (Pang, 2018; Di, 2019). However, TWP directed therapy in combination with basic treatment has not yet been tested clinically. Therefore, we will perform a randomized, controlled trial to evaluate the therapeutic effect of TangWang prescription in delaying the disease progression of patients with NPDR.

## Materials and Methods

### Study Design

This study is designed as a randomized, double-blind, placebo-controlled multicenter clinical trial in accordance with the Helsinki Declaration. This trial is planned to test the hypothesis that TangWang prescription can delay in the progression of DR. A total of 384 participants will be randomly divided into two groups, which will both be administered basic treatments, consisting of oral calcium dobesilate capsules (Ebewe Pharma Ges.m.b.H.Nfg KG, 0.5 g three times per day). All the participants will be randomly assigned to either the treatment group or the control group. The study group will be received the intervention with oral calcium dobesilate capsules + TangWang prescription (one bag twice a day). And the control group will be received the intervention with oral calcium dobesilate capsules + the placebo (one bag twice a day) (Sichuan New Green Pharmaceutical Technology Development Co., Ltd.). Furthermore, diabetes education and diet, as well as rational control of blood glucose, lipids, and pressure will be performed in the two groups according to the American Diabetes Association guidelines.

The central randomization system uses a randomly permuted block design, which includes subject screening, randomization, emergency exposure of blindness, designated drug, drug supply, and other functions. The treatment duration is set at 48 weeks, and the study medications will be labeled by pharmacists according to the randomized list prepared by the central randomization system. The trial schematic flow is illustrated in Figure 1.

**FIGURE 1 F1:**
[figure not shown]
The trial schematic flow.

### Participants

#### Inclusion Criteria

(1) Study participants must meet the diagnostic criteria of type 2 diabetic DR, and the required degree of disease is NPDR (Golozar et al., 2018).(1) Mild NPDR: microaneurysms only(2) Moderate NPDR: one or more of the following:i Hemorrhage (H)/microaneurysms moderate in 4-5 fields;ii or severer in one-field (or) definite intraretinal microvascular abnormality (IRMA) in 1-3 fields.(3) Severe NPDR: one or more of the following:i More severe than moderate NPDRii Severe H/microaneurysms in 4-5 fieldsiii IRMA > moderate in one-fieldiv Definite venous beading (VB) in 2-3 fields.(2) The participants must be between 30 and 70 years old.(3) The participant must sign informed consent forms

Participants who have only one eye can meet the inclusion criteria, and the more severely damaged eye will be chosen when both eyes meet the inclusion criteria. Furthermore, the eye with a better clinical condition will be chosen when both eyes of the participant are at the same clinical stage.

#### Drop-Out Criteria

(1) Participants whose eyes progress to proliferative lesions or undergo laser photocoagulation.(2) Participants whose vision decreases by three or more lines.(3) Participants with certain complications or special physiological changes, which are not suitable for further study. Patients who experience some complications or physiological changes, rendering them unsuitable for further participation.(4) Participants with poor study drug compliance of <80% of the requisite amount or >120% of the prescribed amount of medicine.(5) Participants who break blinding or emergency unblinding of a participant’s information.(6) Participants who use drugs prohibited by the study plan.(7) Participants of reproductive age must receive contraceptive treatments. If the participants are pregnant, they would be considered dropouts.

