### Voluntary Withdrawal of Participants

(1) Participants who do not express the desire to withdraw from the study but cease to accept medication and testing are considered withdrawn.(2) Participants who cannot continue to participate in clinical research for personal reasons; perceive poor efficacy; exhibit intolerance due to adverse reactions; and for economic reasons.

Irrespective of the reason for withdrawal, the case record will be retained. The final test results will be used in the final analysis, and the curative effect and adverse reactions will be analyzed in the full dataset.

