### Secondary Outcome

Change in the number of microhemangioma in DR.Change in the area of microaneurysm bleeding in DR.Change in the area of microaneurysm leakage in DR.Degree of change of macular edema in DR.Change in vision before and after treatment.

Color fundus photography, fundus fluorescein angiography, and coherent optical tomography will be performed every 6x months. Furthermore, the Early Treatment Diabetic Retinopathy Study (ETDRS) international visual acuity test will be performed every month.

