### Statistical Analysis

All statistical tests will be two-sided tests, and a *p* < 0.05 will be considered statistically significant. Quantitative data to calculate the number of cases will be expressed as the mean, median, standard deviation, minimum, and maximum. Qualitative data will list the frequency and percentages. The demography, other baseline characteristics, and efficacy analyses will be analyzed using the full analysis set (FAS), while the per-protocol set (PPS) and the safety analysis will be performed using the safety analysis set (SS).

Quantitative data will be analyzed using the t-test/Wilcoxon rank-sum test, whereas the qualitative data will be analyzed using the X2 test/exact test. The main outcome measures will be analyzed using the X2 test for comparisons between groups, whereas secondary outcome and monitoring measures will be analyzed using the t-test/signed-rank test to compare the groups. The t-test/Wilcoxon rank-sum test will be used to compare the groups. All analyses will be performed using SAS version 9.3.

Three analysis sets will be used for the data analysis. The first is the FAS, which refers to an ideal set of subjects that are as close as possible to the principle of intentionality analysis (including all subjects randomized into the group and treated at least once). If the main variable is missing in any case, the results of the closest observation will be carried forward to substitute the absent test data. We will ensure that the number of participants in each group to be evaluated in the outcome at the end of the study is as consistent as possible before the start of the study. The second dataset is the PPS, consisting of all cases that are following the research plan. This set will consist of the data of participants with good compliance of 80–120% of the prescribed dose. The CRF contains the details of the case, and the main variables can be measured if the baseline variables are not missing, and there is no major violation of the test scheme. The third dataset is the SS, which will consist of the means of all participants who receive at least one treatment after randomization. The demographic, other baseline characteristics, and curative effect analyses, will be performed on the FAS and PPS, while safety will be analyzed using the SS.

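### A loss of three or more lines of vision is a drop-out criterion although change in vision is a secondary outcome, and the article does not fix how these participants enter the vision comparison

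*Protocol article*

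**What the plan says.** All references are to the Protocol article.

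- **Drop-Out Criteria, item 2:** "Participants whose vision decreases by three or more lines".
- **Secondary Outcome:** one of the five outcomes is "Change in vision before and after treatment". The ETDRS "international visual acuity test will be performed every month". Table 2 agrees: vision is recorded at baseline and at each of the 12 visits from week 4 to week 48.
- **Statistical Analysis, test:** "secondary outcome and monitoring measures will be analyzed using the t-test/signed-rank test to compare the groups". The next sentence names the t-test or Wilcoxon rank-sum test for comparing the groups.
- **Statistical Analysis, missing values:** "If the main variable is missing in any case, the results of the closest observation will be carried forward". No rule is given for secondary outcomes.
- **Statistical Analysis, sets:** efficacy is analysed in both the full analysis set (FAS), "including all subjects randomized into the group and treated at least once", and the per-protocol set (PPS), which holds the cases that follow the plan.
- **Voluntary Withdrawal of Participants:** whatever the reason for withdrawal, the record is kept. "The final test results will be used in the final analysis", and "the curative effect and adverse reactions will be analyzed in the full dataset".

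**The concern.** Acuity is both an outcome and a trigger for leaving the study. A participant who meets the three-line criterion at week 20, say, may have no week-48 reading. Belonging to the FAS does not supply one, and the only stated substitution rule covers a different variable.

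If such participants drop out of the week-48 comparison, it describes vision change among people whose vision did not fall far. That is not the effect of TWP on vision in everyone randomized and treated. Mean change would look better than it is in both arms, and the difference between arms would be distorted.

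Vision is the only functional measure among the listed outcomes, and the disease threatens sight. A comparison that can miss the largest losses could hide a benefit or a harm.

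**Working it through.** The article gives no SD, effect or event rate for vision, so there is no stated figure to reproduce. Everything below rests on assumed inputs and shows only how much the choice of reading matters.

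**Inputs.** From the article: a three-line threshold, 12 monthly visits, 192 per arm, two-sided 0.05, and an allowance of up to 15% drop-out. Assumed: three lines = 15 letters (5 per line), mean change at 48 weeks of -3 letters on placebo and 0 on TWP, and a normal change with SD 6 to 8 letters. Week 48 is taken as the *after treatment* time point because treatment lasts 48 weeks.

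**1. Single-look check by formula.** If only participants with change above -15 are compared, the mean in each arm becomes

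m + SD × φ(a) / [1 − Φ(a)], with a = (−15 − m) / SD.

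For SD 8:
- Placebo: a = −1.5, φ = 0.1295, 1 − Φ = 0.9332, ratio 0.1388. Mean = −3 + 8 × 0.1388 = −1.89. Removed: 6.7%.
- TWP: a = −1.875, φ = 0.0688, 1 − Φ = 0.9696, ratio 0.0709. Mean = 0 + 8 × 0.0709 = 0.57. Removed: 3.0%.
- Difference: 0.57 + 1.89 = 2.46 letters against a true 3.00, a loss of 18%.

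The same steps give:

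| SD (letters) | Placebo mean | TWP mean | Difference | Loss |
|---|---|---|---|---|
| 6 | −2.67 | 0.11 | 2.77 | 8% |
| 7 | −2.33 | 0.29 | 2.61 | 13% |
| 8 | −1.89 | 0.57 | 2.46 | 18% |

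**2. Simulation with 12 monthly looks.** Random-slope and random-walk models were run with measurement error and true benefits of 2 to 5 letters. Leaving the participants out lost 5-9% of the difference at SD 6, 10-14% at SD 7 and 16-21% at SD 8. At SD 8 with a 3-letter benefit, the rule removed about 3-5% on TWP and 7-10% on placebo.

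A separate simulation in lines (true difference 0.5 line) agrees. With slope SD 1.5 and noise 0.5 line, the total SD is √(1.5² + 0.5²) = 1.58 lines, or 7.9 letters. It retained 80% of the difference, with removals of 7.5% (placebo) and 3.9% (TWP).

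**3. Power at SD 8, 3 letters, 192 per arm.** With nobody removed, 3 / (8 × √(2/192)) = 3.67 and Φ(3.67 − 1.96) = 0.96. Simulation gives 95-96% with no removal, 88-90% with the participants left out, and 95-96% with their last value kept.

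**4. Direction.** Take equal true means (−0.3 line) but a wider spread on TWP (slope SD 2 against 1 line, noise 0.5). The rule removes 1.2% on placebo and 11.6% on TWP. Leaving them out gives an apparent TWP benefit of 0.41 line (about 2 letters) where the true difference is about zero. Keeping the last value gives 0.04 line.

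**5. If the last value is kept.** The estimate was 94-105% of the truth in one simulation and 91-103% in another. A third, at SD 8 to 12, had a bias of −7% to +6%.

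**6. Likelihood analysis of all monthly values, triggering reading kept.** The estimate was within 1% of the truth wherever it was run (SD 8 to 12). A simple before/after test uses one post-baseline reading and leaves 12 − 1 = 11 unused, which for a drop-out include the reading that met the criterion.

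**The case against.** A reader might infer that the plan does omit these participants and that the vision result is therefore biased toward no effect. The article supports neither statement.

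- **Omission is not stated.** The withdrawal section keeps final results whatever the reason, and the FAS covers everyone randomized and treated at least once. Read together, these can keep three-line losers at their last value, and the mean bias is then small. This stands as a possible reading, but it is not secured. The sentence sits under voluntary withdrawal and follows a list of voluntary reasons, while the three-line rule sits under a separate heading. The carry-forward sentence then names only the main variable.
- **The direction is open.** Shrinkage toward zero needs larger losses on placebo and similar spreads. Step 4 shows the opposite case.
- **Larger figures are not credible here.** At SD 10 to 12 the shrinkage reaches 24-36%. But at SD 10 (measurement SD 4) this one rule would remove 17-23% of placebo participants, and at SD 12 21-29%. That exceeds the 15% allowance for all causes, so those results are set aside.
- **The analysis plan is unseen.** A missing-data rule for a secondary outcome is commonly left to it, and its absence alone would be no finding. The point here is narrower: the article itself states the drop-out rule, the test and a substitution rule confined to another variable, and these interact badly.
- **Carry-forward for vision would nearly remove the mean bias.** This is true. The case for a repeated-measures model is that it also uses the monthly readings and was closer to the truth, not that carry-forward fails.

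**Conclusion.** The concern holds in a limited form. A value of the vision outcome can end follow-up of that outcome, and the article does not settle whether such participants count in the week-48 comparison.

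The two readings give different answers. Leaving them out shrinks a benefit of about 3 letters by roughly 5-20% at SD 6 to 8, or produces a false benefit if the losses fall mainly on TWP. Keeping the last value leaves the estimate within about 10% of the truth. The PPS analysis would probably leave them out in any case, though this too is not stated.

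These sizes depend wholly on the assumed means, SDs and letters per line. The finding concerns a secondary outcome only and says nothing about the primary retinal grade.

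**What to change.** In Statistical Analysis, replace the simple two-group test as the main analysis of vision with the following:

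1. In the FAS, fit a mixed model for repeated measures to change in ETDRS acuity at all 12 monthly visits. Include treatment, visit, treatment-by-visit and baseline acuity, with an unstructured covariance. The week-48 contrast is the estimate.
2. State that the reading that meets the three-line criterion, and any later readings available, are kept as observed data, and that nobody leaves the vision analysis because of that criterion.
3. Report by arm the proportion losing three or more lines at any visit, so that the event is counted as an outcome.
4. Keep the t-test or rank test as a sensitivity analysis, and say how missing week-48 values enter it.

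The cost is one paragraph and a standard SAS program, with no new visits or participants. The downside is reliance on a missing-at-random model. That is reasonable for drop-out triggered by a recorded acuity value, but less certain for other reasons for leaving. No treatment or discontinuation rule is changed.

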We hypothesize that the patients with DR will benefit from TangWang prescription. If successful, this study will provide evidence that the TangWang prescription delays in the progression of DR. Although this protocol uses a rigorous randomized controlled trial to evaluate the effectiveness of the drug, there might also be potential limitations for this study. Firstly, in this multicenter trial, measurement errors in laboratory tests are also inevitable due to different medical equipment in several research centers. Secondly, there might be several individual differences in the subjects, possibly leading to different efficacy of the drug. Thirdly, the long treatment period and tight glucose control may lead to poor patient compliance, which might greatly influence the therapeutic effect. These questions should be explored more thoroughly in the future studies.

DR seriously threatens the vision of working-age people. For patients with NPDR, early treatment is of great significance. In recent years, the prevention and treatment of diabetic retinopathy by Chinese medicine has been a hot research topic. Up to date, this is the largest randomized controlled trial of Chinese medicine for diabetic retinopathy. In this protocol, a double-blind, randomized, placebo-controlled trial will be strictly implemented in multiple research centers. As the gold standard for evaluating drug efficacy, the implementation of the RCT will obtain high-level evidence-based medical evidence, which would fill up the gap in the treatment of early diabetic retinopathy.

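### Poor adherence or prohibited-drug use makes a participant a drop-out, which on a plain reading costs the FAS week-24 or week-48 retinal grades

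*Protocol article*

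**What the plan says.** Under Drop-Out Criteria, item 4 reads "Participants with poor study drug compliance of <80% of the requisite amount or >120% of the prescribed amount of medicine" and item 6 reads "Participants who use drugs prohibited by the study plan". They stand in one list with clinical events, including complications that are described as "rendering them unsuitable for further participation" (item 3).

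Under Voluntary Withdrawal of Participants, the case record is retained whatever the reason for withdrawal, and "The final test results will be used in the final analysis".

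Under Statistical Analysis, the FAS is meant to be close to intention-to-treat, "including all subjects randomized into the group and treated at least once". For missing outcomes: "If the main variable is missing in any case, the results of the closest observation will be carried forward to substitute the absent test data". The PPS has its own adherence rule: "This set will consist of the data of participants with good compliance of 80–120% of the prescribed dose".

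Secondary Outcome and Table 2 place fundus photography, angiography and tomography at baseline, week 24 and week 48. Table 2 has drug returned and counted at every 4-weekly visit.

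**The concern.** Adherence and use of other drugs arise after randomisation and may relate to tolerability, perceived benefit or prognosis. An analysis close to intention-to-treat should therefore keep observing these participants. The PPS already sets aside those outside 80–120%, so item 4 is not needed to obtain a per-protocol analysis. What it appears to add is the end of follow-up, and with it the loss of grades that the FAS could have used. Carry-forward then fills the gap. Before week 24 the only grade scheduled is the baseline one, so the participant is scored unchanged by construction.

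The primary outcome is change in that grade (worse, unchanged or better), so the loss falls on the main comparison. An analysis plan cannot repair it afterwards, because the images would not exist. The Discussion names adherence as a possible weakness: "the long treatment period and tight glucose control may lead to poor patient compliance, which might greatly influence the therapeutic effect".

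**Working it through.** **1. What happens to a participant who meets item 4 or 6.** Putting Drop-Out Criteria, Table 2 and the FAS rule side by side:

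| Time of drop-out | Scheduled grades already obtained | Value in the FAS at week 48 |
|---|---|---|
| Before week 24 | Baseline | Baseline carried forward, so unchanged |
| Week 24 to before week 48 | Baseline, week 24 | Week-24 grade carried forward |
| Judged only at week 48 | All three | Observed, nothing lost |

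The last row shows that timing decides whether item 4 costs anything, and the article fixes no time for the judgement. At two bags a day, a 28-day interval is 56 bags and 48 weeks (336 days) is 672 bags. Judged on one interval, 12 missed bags breach the limit (44/56 = 78.6%). Judged over the whole period, it takes 135 missed bags (537/672 = 79.9%).

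**2. Inputs for size.** From Sample Size Calculation: 8.9% (TWP) and 3.6% (placebo), read here as the shares with a reduced grade, and 192 per arm. The planned difference is 8.9 − 3.6 = 5.3 points. The plan gives no rate for drop-out under items 4 and 6. Its only related figure is the overall 15% allowance, which it applies as 167 × 1.15 = 192.05. (The 167 itself does not follow from the stated rates. That is a separate matter and does not enter here.)

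**3. Equal early drop-out.** Assume that a share f of each arm is dropped before week 24, is scored unchanged, and would otherwise have had the same rates as the rest. Each improvement rate becomes p(1 − f):
- f = 10%: 8.9 × 0.9 − 3.6 × 0.9 = 8.01 − 3.24 = 4.77 points.
- f = 20%: 8.9 × 0.8 − 3.6 × 0.8 = 7.12 − 2.88 = 4.24 points.

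Power for improvement as a yes/no outcome, n = 192 per arm, two-sided 5%, is Φ[(d − 1.96·√(2·p̄(1 − p̄)/n)) / √((p₁(1 − p₁) + p₂(1 − p₂))/n)], where d is the difference and p̄ the mean of the two rates:
- no drop-out: (0.0530 − 1.96 × 0.02471)/0.02456 = 0.187, power 57.4%;
- f = 10%: 52.7%;
- f = 20%: 47.8%.

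**4. Unequal early drop-out.** For worsening, assume a true 10% in both arms, so that there is no real difference.

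| Dropped early | Improvement, TWP − placebo | Worsening, TWP vs placebo |
|---|---|---|
| 15% TWP, 5% placebo | 8.9 × 0.85 − 3.6 × 0.95 = 4.15 points (against TWP) | 8.5% vs 9.5% (favours TWP) |
| 5% TWP, 15% placebo | 8.9 × 0.95 − 3.6 × 0.85 = 5.40 points (slightly favours TWP) | 9.5% vs 8.5% (against TWP) |

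The 1-point gap in worsening is small beside its standard error at 192 per arm: √((0.085 × 0.915 + 0.095 × 0.905)/192) = 2.9 points.

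**The case against.** The strongest objection is that no sentence says that visits or imaging stop when a criterion is met. Follow-up after discontinuation is something an article may leave to the full protocol, and the final test results mentioned under Voluntary Withdrawal of Participants could mean an exit assessment. This stands as a limit: the end of follow-up is inferred. It is still the plain reading. Item 3 speaks of unsuitability for further participation, the sample size is inflated for drop-outs as though they were lost to evaluation, and nothing shown provides for grading afterwards. An exit grade, if taken, would replace the baseline grade but would still come before week 48.

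Item 4 can also be read as total adherence judged at the end, and then it loses no grade. That is fair, but the text does not say so, and item 6 would remain.

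A reader might go further in four ways that the documents do not support:
- *The trial cannot estimate the effect of assigning TWP.* Every randomised and treated participant stays in the FAS, and anyone dropped after week 24 contributes an observed week-24 grade.
- *The rule creates a false benefit for TWP.* The same 15%/5% split that favours TWP on worsening works against it on improvement, so the net direction is unknown.
- *A fully adherent patient could breach 80% when visits are far apart.* That needs an assumed 28-day supply, and the article states neither the supply nor how adherence is counted.
- *The rule is certain to be triggered.* The Discussion says only that compliance may be poor.

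**Conclusion.** The point holds as a stated rule with an avoidable cost. Items 4 and 6 make a participant a drop-out for behaviour after randomisation, item 4 repeats a limit that the PPS already applies, and on a plain reading the FAS then relies on a carried-forward grade where an observed one could have been had. Neither the fact nor the frequency of the loss is certain.

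With equal early drop-out of 10% or 20% per arm, the planned 5.3-point difference falls to 4.8 or 4.2 points. With unequal drop-out, bias can run either way. These figures rest on assumed drop-out rates, on all drop-out coming before week 24, and on dropped participants resembling the rest. They show scale and are not predictions.

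**What to change.** Reconcile Drop-Out Criteria with the FAS definition in Statistical Analysis. State that participants who meet item 4 or 6:
- are excluded from the PPS only;
- keep the scheduled week-24 and week-48 retinal grading unless they withdraw consent;
- enter the FAS with their observed grades.

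State also that the 80–120% figure is calculated cumulatively over the treatment period. Whether study drug continues in these participants is a separate decision for the sponsor, and this change does not touch it.

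The cost is protocol wording, since the imaging is already in the schedule. Sites must keep following these participants, and the FAS estimate will include non-adherent patients, as an analysis close to intention-to-treat intends.
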